## Abstract

**Background:**

Dual sensory loss (DSL) has a negative impact on health and wellbeing and its prevalence is expected to increase due to demographic aging. However, specialized care or rehabilitation programs for DSL are scarce. Until now, low vision rehabilitation does not sufficiently target concurrent impairments in vision and hearing. This study aims to 1) develop a DSL protocol (for occupational therapists working in low vision rehabilitation) which focuses on optimal use of the senses and teaches DSL patients and their communication partners to use effective communication strategies, and 2) describe the multicenter parallel randomized controlled trial (RCT) designed to test the effectiveness and cost-effectiveness of the DSL protocol.

**Methods/design:**

To develop a DSL protocol, literature was reviewed and content was discussed with professionals in eye/ear care (interviews/focus groups) and DSL patients (interviews). A pilot study was conducted to test and confirm the DSL protocol. In addition, a two-armed international multi-center RCT will evaluate the effectiveness and cost-effectiveness of the DSL protocol compared to waiting list controls, in 124 patients in low vision rehabilitation centers in the Netherlands and Belgium.

**Discussion:**

This study provides a treatment protocol for rehabilitation of DSL within low vision rehabilitation, which aims to be a valuable addition to the general low vision rehabilitation care.

**Trial registration:**

Netherlands Trial Register (NTR) identifier: NTR2843

## Background

As a result of the aging of the Western population, impairments of hearing and vision caused by age-related degeneration of the senses (e.g. presbyacusis and macular degeneration) are expected to increase rapidly [1,2]. A relatively large number of older adults suffer from concurrent impairments in hearing and vision, also known as dual sensory loss (DSL) [3-8]. Among older adults, the prevalence of DSL ranges from 4.7 - 9.7% in the general population and from 20-45% in those in nursing homes, hospitals and low vision rehabilitation [1,9-13].

DSL has a detrimental effect on a patient’s health and well-being in relation to, for example, communication, social participation, depression, cognition, functional disability, health-related quality of life, self-rated health and mortality [3-5,13-22]. Presumably, DSL also affects communication partners. Studies on single sensory loss show that communication partners experience caregiver burden, depressive symptoms, disability, tension in the relationship and show increased reliance on informal care [23-27]. Besides support from friends and family, sensory impaired patients also rely on support from community services [26,28] and sensory loss is associated with high societal costs [29-31].

Two main issues affect the lives of DSL patients. First, DSL impairs proper use of hearing aids. The complexity and small size of hearing aids makes handling and maintenance difficult for DSL patients. Examples of difficulties are inserting the hearing aid or ear mold in the ear, seeing the controls, or replacing batteries (glare from reflective surfaces may interfere with seeing the battery polarity) [32]. Therefore, concurrent visual impairment could (in addition to other age-related discomforts such as tactile sensitivity and manual dexterity) impede the handling and maintenance of hearing aids. This may result in misuse and/or underuse of hearing aids [32]. Studies among hearing-impaired older adults reported a low rate of hearing aid use [33-35]. Although older adults with DSL are in great need of amplification (because of decreased lip-reading ability due to visual impairment) [32], many patients experience problems with handling hearing aids or do not use them at all despite their well-known benefits on e.g. on quality of life [36]. Since DSL patients are less able to compensate with visual cues, they depend heavily on their (aided) hearing. Therefore, improper and/or non-use of hearing-aids may lead to result in a detrimental effect on health.

Second, DSL impairs communication as both good visual and hearing acuity enhance speech understanding. In DSL patients, age-related hearing loss reduces the ability to discriminate speech. In turn, a visual impairment reduces the perception of visual cues supporting speech understanding, such as looking at the speaker’s face/mouth and other bodily movements and gestures [32,37-40]. Although use of hearing aids has a positive effect on communication, problems persist in common noisy listening situations where hearing aids are inadequate [41]. When communication frequently fails, negative experiences can lead to avoidance of conversations and so-called ‘communication break downs’. These break downs are highly distressing and can cause feelings of loneliness, social isolation and depression [42-45].

Although DSL patients would benefit from rehabilitation to cope with these problems, integrated rehabilitation of DSL is scarce. In current practice, rehabilitation of sensory impairments in the aging population is divided into separate rehabilitation services for impairments in vision (low vision rehabilitation centers) and in hearing (audiology centers and hearing aid providers). Concurrent hearing impairment could affect the success of low vision rehabilitation [12] and vice versa. Moreover, healthcare providers do not automatically deal with impairment of the ‘other sense’, which may lead to less effective rehabilitation. Therefore, Saunders & Echt (2007) recommended to combine these two independent services [46]. In fact, the development and systematic evaluation of multidisciplinary integrated rehabilitation of DSL in older adults (i.e. communication training in which communication partners are involved) is considered one of the most urgent research needs in health care [46-48].

This paper reports on the development of a ‘Dual Sensory Loss-protocol’ (DSL protocol) designed for occupational therapists (OTs) working in the field of low vision rehabilitation, which focuses on maximal use of remaining hearing and vision. The protocol presents an integrated treatment of DSL for older adults within low vision rehabilitation. In addition, the design and methodology of a randomized controlled trial (RCT) to evaluate the effectiveness and cost-effectiveness of this protocol is described.

## Methods/Design

### DSL protocol

#### Development

In the development of the DSL protocol, literature was reviewed, and patients and professionals were consulted. First, the literature was reviewed on the topic of rehabilitation of DSL, and on existing interventions or recommendations on rehabilitation of DSL [42,46,49-57] and audiological rehabilitation [41,58]. Results of the literature review and content of the protocol were discussed in interviews and two focus group discussions with professionals in low vision and audiological rehabilitation. Professionals participating in the focus groups were: two OTs, a social worker, two clinical physicists and three psychologists (two from the field of low vision and one from audiological rehabilitation) and an audiologist. These professionals discussed the design (e.g. manual, checklist, use of a hand-out card with tips and recommendations for communication partners) and content of the DSL protocol (e.g. the importance of raising awareness, provision of information on hearing assistive devices) and also came up with specific suggestions (e.g. referral to audiological centers, social work or peer groups). In these discussions, it was decided that the DSL protocol would be a new intervention on top of usual care of low vision, after remaining eyesight is optimized as much as possible.

However, because professionals may have some (work-related) bias, DSL patients and their communication partners were also consulted [58]. Three DSL patients (aged 50+ years) and one patient’s partner were interviewed during home visits. The patients were invited to participate by the Dutch Foundation for the Deafblind and by a participating low vision rehabilitation center (Bartiméus). In all patients the cause of deaf-blindness was Usher syndrome. Patients were asked what problems they generally encountered, and also provided advice for new patients; e.g. they recommended patients that patients consult other patients for help and also involve the family in patient care.

A draft of the DSL protocol was sent to all professionals involved; in two feedback rounds, they were asked to provide comments/suggestions on the draft.

The DSL protocol provides information on DSL. However, because of the aim to implement the protocol in low vision rehabilitation centers, it also focuses on the gap in knowledge related to audiology and rehabilitation in that field.

#### Topics described in the DSL protocol

In the DSL protocol, rehabilitation is divided into three chapters (Chapter 1: Hearing aids; Chapter 2: Optimal use of the senses; living environment & hearing assistive devices; Chapter 3: Communication and coping with DSL). Chapter 1 of the DSL protocol includes information on audiology and the benefits/limitations of hearing aids, and also focuses on the proper use/maintenance of hearing aids. The chapter starts by informing the patient/communication partner about both vision and hearing loss to raise recognition, awareness, knowledge and understanding of sensory impairments. Patients/communication partners are informed about the benefits/limitations of hearing aids in order to develop realistic expectations and, for the communication partner to gain understanding of the situation. Note that care must be taken in addressing unrealistic expectations, as too low expectations could demotivate or discourage patients from using hearing aids [59].

Then, the DSL protocol focuses on the proper and optimal use of hearing aids. Although correct use of hearing aids is a prerequisite, it cannot be presumed. Hearing aid users benefit from training [54]; training in how to handle, manipulate, insert and remove hearing aids and test batteries enhances hearing aid use and maintenance. However, older adults may need additional instruction time to acquire these skills [60]. Because of the expected difficulties related to the visual impairment and limited training from hearing aid suppliers, exercises to teach these procedures to DSL patients and/or proxies are included in the first chapter of the DSL protocol. OTs teach and train patients (or communication partners) how to handle and maintain hearing aids with the use of low vision devices (e.g. stand magnifiers or CCTV) [46].

In the second chapter, the DSL protocol focuses on optimal use of the senses by improvement of the living environment in relation to lighting, acoustics and proximity, and the use of low vision and hearing assistive devices [46,61,62]. To improve understanding of speech, the OT advises to make minor adaptations to optimize the living environment to improve visibility and audibility (if required). For example, an OT may, for example, recommend the patient to reduce the distance between communication partners (proximity) to improve visibility and audibility [52]. To enhance acoustics, the OT may, for example, recommend to reduce background/room noise and to reduce reverberation with sound-absorbent furnishings such as heavy curtains, carpeting and cushions [46]. Depending on the situation, OTs may also advise patients on acoustics, lighting and proximity. Subsequently, OTs provide advice and information on assistive devices for hearing and vision, and about the interconnectivity of the devices.

Communication and coping with DSL is the focus of the third chapter; it stimulates use of communication strategies (patients and communication partners) and social participation, it also discusses problems with energy/fatigue, and provides information on peer support. Communication difficulties and decreased social activity of DSL patients have a negative impact on wellbeing [45]. Use of effective communication strategies such as seeing the speaker (use of facial cues by face-to-face orientation and visual attention) might enhance communication in difficult situations [63]. These strategies focus on optimizing auditory-visual speech perception by enhancing face-to-face communication, effects of high visual contrast, glare, illumination and distance on visual-speech perception [37]. Although the severity of the visual impairment of DSL patients affects their ability to ‘see the speaker’, simulations have shown that even severely visually impaired persons are able to use visual cues up to some extent for speech reading [37,39,63] and that DSL patients found learning new strategies useful [56]. Parts of an existing and effective communication training program for hearing-impaired older patients and their hearing communication partners, developed by Kramer et al. (2005) have been incorporated in the DSL protocol. In this training, older adults with hearing loss only (and their hearing communication partners) learned to use communication strategies [41]. Others have also proposed involving communication partners in the training of communication strategies [55]. Despite the fact that DSL patients regularly experience communication difficulties, communication partners are often unaware of these problems. OTs address communication difficulties and teach DSL patients and communication partners to use effective communication strategies in addition to hearing aids, which may also improve their quality of life. Subsequently, OTs encourage the patient to bring these newly learned strategies into practice, and to participate in social activities that they previously enjoyed, but ceased because of communication difficulties induced by DSL [49]. Thirdly, another problem confronting DSL patients is fatigue. DSL patients often feel exhausted, especially in communication, when concentration and effort is required for listening and understanding [56]. OTs address the problem of fatigue and discuss management of the energy balance. Finally, OTs provide information on patient organizations and peer groups which can provide some support.

#### Two parts of the DSL protocol

The protocol is divided into two parts: i) a comprehensive guidebook for the professional, and ii) checklists for each patient. The guidebook provides background information, materials and comments on each exercise. Materials include a CD, DVD, large printed handouts (font 14, light-yellow colored matte/non-glossy paper), information on patient organizations, a large printed picture of a loop system sign, information on financial compensation for assistive devices, a handout with instructions on hearing aid use and maintenance, and handouts with communication strategies for patient and communication partners.

The second part of the protocol consists of checklists for each patient with exercises and instructions, which follow the three chapters of the guidebook. Items of the checklist are:

Introduction

1) Discuss goal and design of treatment

2) Check severity of vision and hearing loss

3) Check available low vision and hearing aids

4) Check if the patient has comorbidity

5) Create awareness with the patient of his/her dual sensory loss

6) Create awareness of the communication partner about dual sensory loss (CD)

Chapter 1: Hearing aids

7) Give information on hearing aids and discuss realistic expectations

8) Discuss experiences and problems with hearing aids

9) Check working of hearing aid, batteries and tube

10) Check amplification of hearing aid

11) Check replacement of hearing aid and ear mold

12) Check visibility of hearing aid, advise on use of low vision devices if necessary

13) Check the possibilities of the hearing aid, such as settings/modes and programs

14) Check skills in hearing aid use and manipulation of controls

15) Check batteries and battery replacement

16) Mark hearing aid

17) Dry clean ear mold

18) Wet clean ear mold

*Chapter 2: Optimal use of the senses: living environment* &*hearing assistive devices*

19) Lighting for speech reading

20) Advice on acoustics for speech intelligibility

21) Use of loop systems in public buildings

22) Use of subtitles and spoken subtitles

23) Check whether the patient would benefit from other hearing assistive devices

Chapter 3: Communication and coping with DSL

24) Address problems related to fatigue and energy balance

25) Use of communication strategies by the patient (handout)

26) Use of communication strategies by communication partner (handout)

27) Discuss the use of communication strategies on the basis of propositions

28) Address DSL (vision and hearing impairment) to the speaker

29) Ask speaker for clarification

30) Discuss communication strategies using specific questions

31) Provide information on patient organizations and peer groups

Home assignment

a) Watch the DVD ‘Hearing and being heard’ on the use of communication strategies, together with the communication partner. Discuss the situations on the DVD using questions.

b) Attend a social activity, to apply the new skills and communication strategies.

The OT will go through the checklist in 3–5 sessions at the patient’s home; participation of the communication partner is strongly recommended. The sessions are divided in two parts of 30 minutes each, separated by a break of 15 minutes. This takes into account, the length of the sessions, as well as the rapid fatigue and decreased ability of older adults with DSL to concentrate for longer periods of time. The exact number of sessions needed to go through the checklist depends on the abilities/needs of the individual patient. We anticipate the (valuable) participation of communication partners, since communication is interactive and relies on the conversational abilities of both communication partners.

#### Training of OTs and pilot-study

To use the DSL protocol, OTs need training. For the current RCT to test the effectiveness of the DSL protocol, OTs from two participating rehabilitation institutions were offered a one-day training in the DSL protocol on October 18th, 2011. The first part of the training was provided by an audiologist and involved background information on audiology. Subsequently, a hearing aid provider gave instructions on the use and maintenance of hearing aids, exercises on hearing aid use, and gave information and a demonstration on hearing assistive devices. In the second part of the training, a speech therapist taught the OTs how to teach patients and proxies to use adequate communication strategies, e.g. with the use of role play. In role play, special glasses and earmuffs were used to simulate vision and hearing loss of DSL patients. The training was filmed and later on three other OTs were later trained with using this film as part of their training.

In a limited pilot study (before the start of the RCT) OTs went through the DSL protocol with a DSL-patient in a real-life situation. The results of this pilot study were evaluated in three meetings with the OTs and, subsequently, a few clarifying adaptations were made to the protocol.

### Design and methodology of the RCT

#### Study design

A two-armed international multicenter parallel RCT will be conducted to evaluate the health effectiveness and cost-effectiveness of the DSL protocol from a societal perspective in low vision multidisciplinary rehabilitation institutions in the Netherlands and Belgium. The design of the trial is shown in Figure 1.

**Figure 1 F1:**
[figure not shown]
Design of the trial.

The study is approved by the Medical Ethical Review Committee of the VU University Medical Center (the Netherlands) and the Ethical Committee of University Hospitals UZ/KU Leuven (Belgium) according to the principles of the Declaration of Helsinki. The trial is registered at the Netherlands Trial Register (http://www.trialregister.nl, identifier: TC = 2843).

#### Study population

Prior to the trial, patients of low vision rehabilitation were screened for eligibility. A short, large-print questionnaire on hearing problems and hearing aid ownership was sent to all patients (aged >50 years) who received low vision rehabilitation between January 1 and October 31, 2012. Addresses were derived from the patient information databases of the rehabilitation institutions. After two weeks, patients who did not fill in the questionnaire were telephoned about the questionnaire and in case the patient was not able to fill in the questionnaire due to low vision, the questions were administered orally by telephone. More details on the screening and the results of the screening are published elsewhere [11].

Patients who experience hearing problems and are in the possession of a hearing aid will be invited to participate in the RCT. Hearing aid owners will be invited to participate because hearing aids, and making optimal use of hearing aids, are an important part of the DSL protocol. In addition, by selecting hearing aid owners with hearing problems by using information from the questionnaire, patients with both objective hearing loss (reimbursement of hearing aids from a hearing loss of at least 35 dB) and self-reported hearing disability will be selected; these patients are expected to be motivated and the most suitable for rehabilitation [48]. Moreover, due to time constraints, it is not possible to wait for patients to fit hearing aids in order to be able to take part in the trial; this procedure may take months due to the required testing period and possible reimbursement.

Written information will be sent to eligible patients and informed consent will be signed prior to inclusion. It is expected that about 1500 patients need to be screened to include 124 eligible participants in the trial. Patients who are unable to comprehend or respond to questions due to cognitive impairment, or have insufficient knowledge of the Dutch language, will be excluded from the study. Table 1 summarizes the inclusion/exclusion criteria.

**Table 1 T1:** Inclusion and exclusion criteria for the randomized controlled trial

***Inclusion***	***Exclusion***
Age ≥ 50 years	Cognitive deficits
Visual impairment (low vision rehabilitation)	Deaf persons
Hearing impairment:	Insufficient knowledge of the Dutch language
• Self-reported hearing problems*	
• Hearing aid ownership (mean pure tone thresholds at 1000, 2000 and 4000 Hz >35 dB the Netherlands, and >40 dB Belgium)	

*See Vreeken et al. 2013 [11].

#### Randomization

After baseline measurements, participants will be randomly allocated (stratified by therapist) to either the intervention or control group, by means of computer-generated tables. Trained OTs employed by the participating low vision multidisciplinary rehabilitation institutions in the Netherlands and in Belgium will provide therapy for older adults with DSL and their communication partner (i.e. the intervention group) according to the newly developed DSL protocol. To prevent unequal distributions of participants in the control and intervention groups among OTs, participants will be stratified within working areas of OTs before randomization resulting in eight strata, one for each of the eight participating OTs (four OTs from Bartiméus, two OTs from Visio and two OTs from Blindenzorg Licht en Liefde). Block randomization will be performed in blocks of two to ensure equal group sizes in each stratum. Randomization will be performed by an independent researcher using a computer-generated allocation scheme so that the researcher who will analyze the data is blinded (trained research assistants will enter all data into a laptop computer using codes). All participants will be informed about the allocation. In case a participant is allocated to the treatment group, an email will be sent to inform the designated OT. Treatment will take place in the participant’s home in 3–5 appointments, depending on the individual needs of the participant and/or proxy. All participants have received low vision rehabilitation and hearing aid fitting before entering the study. Using a waiting list procedure, participants in the control group will be offered treatment after 3-month follow-up measurements.

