Second, due to budgetary restrictions it was not possible to provide information on the long-term effects. Third, blinding of participants and OTs is not possible since no placebo treatment is included in the study to account for the placebo effect. Participants may report change as a result of simply meeting with an empathetic professional each week to discuss problems. Therefore, the effect of the DSL protocol is the total difference between groups, including both treatment and associated placebo effects. This has both advantages and disadvantages: a disadvantage is that the pure effect of the DSL protocol’s content remains unclear whereas, on the other hand, reality is best reflected. This pragmatic trial provides the best reflection of the likely rehabilitation outcome in actual practice.

This study provides useful information on DSL. Also, if the trial shows the DSL protocol to be effective, this will allow multidisciplinary low vision rehabilitation centers to provide an evidence-based treatment protocol for DSL patients. The DSL protocol will be an important tool for OTs to assist their older patients with DSL in the use of hearing aids, to maximize use of the senses, and to teach patients and/or communication partners specific skills to improve communication.

However, DSL needs more attention in other care settings (besides low vision rehabilitation), such as nursing homes and audiology rehabilitation. It is estimated that about 2% of the elderly who consult a hearing healthcare professional experience such visual impairment to such extent, that it limits the perception of facial cues for communication [54]. Although future research on DSL in audiology care is recommended, rehabilitation of DSL in the setting of audiology care requires even more effort. Hearing impairment in the elderly occurs much more frequently than visual impairment. Therefore, DSL in audiology rehabilitation is less common, so that more patients need to be screened to detect patients with DSL. In addition, low vision and hearing rehabilitation is organized in different ways. For example, in the Netherlands, many older adults with hearing loss in the Netherlands do not consult a multidisciplinary audiology rehabilitation center but go directly to a hearing aid dispenser; this occurs much less with low vision.

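### A fixed block size of two within each therapist stratum of an open trial makes up to half of the allocations predictable; randomly varied blocks would remove most of this cheaply

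*Protocol article*

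**What the plan says.** All of the design features come from the Randomization section of the protocol article, unless noted.

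- **Strata:** therapists' working areas, "resulting in eight strata, one for each of the eight participating OTs".
- **Blocks:** "Block randomization will be performed in blocks of two to ensure equal group sizes in each stratum". The size is fixed and is printed in the article.
- **Disclosure:** "All participants will be informed about the allocation". For the therapist: "In case a participant is allocated to the treatment group, an email will be sent to inform the designated OT".
- **Blinding:** the Discussion accepts that "blinding of participants and OTs is not possible since no placebo treatment is included in the study".
- **Who randomises:** "Randomization will be performed by an independent researcher using a computer-generated allocation scheme so that the researcher who will analyze the data is blinded". The purpose given is to blind the analyst.
- **Timing:** consent comes before inclusion (Study population), and allocation follows the baseline measurements.

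Baseline is a structured face-to-face interview at home, conducted by research assistants (Data collection). The treatment effect is the allocation-by-time interaction (Statistical analysis), so baseline values enter the estimate directly.

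**The concern.** Concealment needs two things: the list must be hidden, and its next entry must not be deducible from entries already revealed. The independent researcher and the computer-generated scheme serve the first. A fixed block of two undermines the second, because once the first member of a pair is known, so is the other.

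Two steps come before randomisation and could be affected by such knowledge. One is the choice of whom to invite or visit next in a therapist's area. The other is the baseline interview, which relies largely on self-report. Randomising after baseline protects that interview only if the coming allocation cannot be foreseen. The mixed model uses measured baseline values, but it cannot correct for unmeasured differences between patients, or for baseline answers that were themselves influenced.

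**Working it through.** **Inputs.** Total 124, or 62 per arm (Study population; Sample size). Eight strata, so 124/8 = 15.5 patients per stratum on average. Block size 2, ratio 1:1 (Randomization). The plan gives no figure for predictability, so there is none to reproduce.

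**Certain allocations, blocks of two.** In a stratum of n patients, every second entry is determined by the one before it, which gives floor(n/2) certain entries. Over all strata the count is (124 − k)/2, where k is the number of strata with an odd size.
- All strata even (k = 0): 124/2 = 62, or 50%. This is the maximum.
- Four strata of 15 and four of 16 (k = 4): 4×7 + 4×8 = 60.
- All strata odd (k = 8): (124 − 8)/2 = 58, or 47%.

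**Correct guesses, blocks of two.** The certain entries are always right and the others are right half the time. At the maximum this is 62 + 62/2 = 93 of 124, or 75%. With all strata odd it is 58 + 66/2 = 91, or 73%.

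**Alternatives.** Fixed blocks were enumerated exactly. Varied blocks were simulated on strata of 16, with a guesser who knows which sizes are possible but not which one is in use.

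| Scheme | Certain in advance | Correct guesses |
|---|---|---|
| Fixed 2 (plan) | 50% | 75% |
| Fixed 4 | 33% | 71% |
| Fixed 6 | 25% | 68% |
| Varied 2 and 4 | about 10% | about 72% |
| Varied 4 and 6 | about 6% | about 68% |
| Simple randomisation | 0% | 50% |

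The main gain from varied blocks of 4 and 6 is in certainty, which falls from one allocation in two to about one in sixteen. The guess rate improves only modestly.

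**Price in balance.** Blocks of two leave a difference of at most 1 per stratum; blocks of 4 and 6 leave at most 3. In the extreme case, all eight strata differ by 3 in the same direction. The total difference is then 24, or 74 against 50. Efficiency relative to equal arms is 4×74×50/124² = 14,800/15,376 = 96%. Starting from 80% power, 1.960 + 0.842 = 2.802. Multiplying by √0.9625 = 0.981 gives 2.749, and 2.749 − 1.960 = 0.789, which is a power of about 78.5%. Any realistic imbalance costs less.

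**The case against.** The strongest reply is that prediction needs one person who knows the block size, the order of entry in the stratum and the preceding result, and who can also influence the next entry or the baseline interview. The article does not place all of this in one role. Participants are told their own allocation only. Therapists hear only of treatment allocations and are not described as inviting, consenting or assessing. Candidates come from a questionnaire sent to all patients in a fixed calendar window, and the baseline interview is structured and entered directly into a laptop. The plan also gives a reason for its choice: "to ensure equal group sizes in each stratum".

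Much of this stands. Three stronger readings are tempting and are not supported:

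- **That concealment is defeated, or that selection took place.** The article does not say who learns earlier allocations. A condensed article may leave that to the full protocol, so its silence is not a finding. Follow-up includes items for the intervention group only (Table 2), so whoever administers them learns the arm, but only about three months later.
- **That exactly 62 allocations are determined.** That is a ceiling, reached only if every stratum has an even size.
- **That the pairing unblinds the analyst.** Data are entered under codes, and nothing says that the order of allocation reaches the analyst.

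The reply does not remove the stated choice itself. Neither an independent list-holder nor randomisation after baseline stops the second entry of a pair from being deduced, and larger blocks would give nearly the same balance per therapist.

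**Conclusion.** The point holds as an avoidable weakness in allocation concealment. At most 62 of 124 allocations (58 at the least, if every stratum has an odd size) are certain to someone who knows the block size and the preceding allocation in the stratum. That person guesses correctly about 75% of the time.

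These figures assume 1:1 pairs, full enrolment to 124 and one-at-a-time allocation within each stratum. If a whole stratum were randomised in one batch after all its baseline visits, prediction would be moot, but the article does not say this. The figures describe what an informed person could predict, not what anyone did. The size of any resulting bias cannot be derived from the document.

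**What to change.** Keep stratification by therapist. Replace the fixed pairs with randomly permuted blocks whose size varies at random between 4 and 6. The independent researcher should hold the block sizes. State that block sizes and prior allocations are withheld from those who invite, schedule or interview participants, and do not publish the sizes while recruitment is open.

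The cost is a new computer-generated list and a possible imbalance of at most 3 patients per therapist instead of 1. Certain allocations fall to about 6% and correct guesses to about 68%. The loss of power is negligible: about 1.5 percentage points even in the extreme case shown above.
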